### Specific aims

To derive a three-part triage algorithm to better predict (a) treatment priority; (b) medical risk and thus need for in-hospital treatment; (c) post-acute care needs of patients at the earliest time point of ED admission in a large and unselected population of medical patients.

This is done by development of three algorithms for assessing:

(a) Treatment priority (high vs. low priority). This will be based on the MTS as the current state of the art tool, and other clinical variables and blood biomarkers (Figure 
1B). This algorithm should help to correctly prioritize patients in a crowded ED setting and allocate resources to patients needing them first.

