### Endpoints

To improve management of patients at the earliest time point of ED admission, we aim to develop a triage algorithm based on three distinct decision rules for (a) assessment of triage priority, (b) need for hospitalization and (c) post-acute care needs as shown in Figure 
1. We therefore have three distinct main endpoints:

(a) Initial triage priority adjudicated by two independent ED physicians. Similar to a previous study
[37], the physicians will evaluate what the real degree of urgency (“Goldstandard”) would have been, based on the ED data, results of diagnostic tests, and the final diagnosis. Specifically, the main question for the adjudicators will be “*under difficult circumstances*, *what is the maximum possible time that this patient would have been able to wait before being seen*?” with options of “patient could not wait”, 10 minutes, 30 minutes, 90 minutes, or 3 hours. To further standardize the adjudication, we have developed examples as demonstrated in Figure 
2. We will collapse the initial 5 priority categories into 2 categories (i.e. low [more than 10 min, class 3, 4 or 5] vs. high priority [less than 10 min, class 1 or 2]). The 2 adjudicators will answer this question in regard to a medical prognostic focus and to a patient comfort focus (i.e. pain). In case of disagreement, a third independent physician will review the case until consensus is reached.

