### Statistical considerations and sample size

The purpose of this study is to develop an improved triage tool based on three distinct algorithms for (a) estimation of treatment priority (model 1), (b) prediction of medical risk (model 2) and (c) risk of post-acute care needs (model 3). For this purpose we have defined three distinct binary endpoints (i.e. high vs. low triage priority, adverse medical outcome within 30 days, post-acute care need) for which independent prediction rules will be developed using a similar approach for each one. However, based on the published literature, different candidate parameters will be considered as predictors for inclusion into the models.

In brief, for each algorithm we will select a parsimonious set of parameters from a comprehensive list of candidates including vital signs, clinical / socio-demographic predictors, blood markers, the MTS and the PACD. For blood markers we will focus on proADM and urea as the most established prognostic markers; however, we will also consider other markers for completion based on the availability of routine data (Table 
1). We will use multivariable logistic regression analysis and different selection techniques including stepwise regression, Lasso among others
[72]. We will also compare the non-parametric CART analysis to decide if a simpler algorithm would qualify. Improvements in the area under the receiver operating curve (AUC) and reclassification statistics will inform about the benefit of adding parameters to the model
[72,73]. We will apply split sample validation (training and validation set with a ratio of 1:1) and present goodness of fit statistics to assess robustness and internal validity. Based on these results, we will derive weighted admission risk scores for the three main models, which can be used for later decision making (Figure 
1). We will also look at subgroups to investigate differences in performance between main diagnoses and socio-demographic factors (age, gender) by inclusion of interaction terms into the logistic models.

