For our model 1 (treatment priority), we will use adjudicated initial triage priority as the endpoint of interest (low vs. high triage priority) as defined above. As the MTS is well established for this purpose, we will first investigate the ability of the MTS to identify high priority subjects. We will then investigate whether addition of clinical parameters, vital signs and blood markers improve the MTS using statistical approaches outlined above. In a second step, we will investigate the performance of the MTS in subgroups of patients, i.e. stratified by initial admission diagnosis (e.g. myocardial infarction, congestive heart failure, infection, falls, lung embolism), by main clinical complain (e.g. dyspnea, fever, cough, pain) and by age quartiles, we will include interaction terms to study whether the association of the MTS and / or biomarkers varies across subgroups (effect modification). If significant effect modification is found, we will adapt the risk score to certain admission diagnoses.

For our model 2 (adverse outcome within 30 days) we will focus on death or ICU admission as the main outcome, in accordance with established risk scores (such as the pneumonia severity index or the CURB65 score)
[9]. In previous research
[18,27,34,35] we found that specific blood biomarkers (i.e. proADM) have very high prognostic accuracy in the range of clinical risk scores, and that this is true across different medical conditions. However, other “baseline” factors, such as age and comorbidities are likely providing prognostic information beyond that of blood markers. Thus, it is a promising approach to combine these factors in a combined risk model.

Our model 3 (post-acute care needs) will focus on care needs in patients after hospital discharge. The PACD score was developed for this purpose. However, the PACD focuses mainly on care needs of patients prior to hospital admission and availability of help in the home setting, but not as much on the current medical situation. It is therefore possible that addition of parameters reflecting the severity of disease (vital signs, blood markers) or the nutritional condition (blood markers) further improves its accuracy. We will therefore start with the PACD and investigate whether addition of other parameters significantly improves its accuracy as outlined above.

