## Discussion

### Potential limitations and bias

Treatment priority as adjudicated by the attending physicians at ED discharge is not a “hard” endpoint and may be subject to variation due to different levels of experience of physicians. Nevertheless, we have developed guidelines (Figure 
2) that will help to standardize adjudication based on previous research in this field
[37]. In addition, we will also look at other more objective endpoints (i.e. mortality, ICU admission, LOS). We will also collect information about physicians (years of experience, age, baseline “opinion” about risk scoring) and will thus be able to adjust the analysis accordingly. Also, physicians and nurses will not be blinded to the MTS, PACD and the risk assessment overall and thus may adapt their priority recommendation accordingly. This may overestimate the performance of the triage scoring systems. In terms of other blood markers and clinical parameters to improve the MTS, this bias will be minimal. Within this observational quality control project, we will not be able to demonstrate whether improved triage of patients translates into better management and improved outcomes; for this reason, we plan a second randomized controlled trial. While most prognostic blood markers (including proADM) are now commercially available within 1–3 hours, faster point-of-care tests are currently being developed that would enable measurement of marker within minutes, similar to a glucose measurement. This will further improve bedside use of these markers in the near future trial.

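### Model 1 sorts patients at a 10-minute cut-off but may retain markers that take 1–3 hours, and the only marker-free version specified is the MTS alone

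*Protocol article*

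**What the plan says.** **Purpose and time of use.** Under Specific aims, the protocol article sets out to predict treatment priority, medical risk and post-acute care needs "of patients at the earliest time point of ED admission in a large and unselected population of medical patients". Of the treatment-priority algorithm it says: "This will be based on the MTS as the current state of the art tool, and other clinical variables and blood biomarkers".

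**Outcome.** Under Endpoints (a), adjudicators judge how long the patient could have waited. Apart from the option that the patient could not wait at all, the choices are "10 minutes, 30 minutes, 90 minutes, or 3 hours". The five classes are then collapsed: "low [more than 10 min, class 3, 4 or 5] vs. high priority [less than 10 min, class 1 or 2".

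**Predictors and selection.** Under Statistical considerations and sample size: "For blood markers we will focus on proADM and urea as the most established prognostic markers". For model 1 the MTS is assessed alone first, and then: "We will then investigate whether addition of clinical parameters, vital signs and blood markers improve the MTS". The criterion for added predictors is: "Improvements in the area under the receiver operating curve (AUC) and reclassification statistics will inform about the benefit of adding parameters to the model". Weighted admission risk scores are then derived for the three models.

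**Turnaround.** Under Potential limitations and bias: "While most prognostic blood markers (including proADM) are now commercially available within 1–3 hours". The sentence goes on to say that point-of-care tests giving results within minutes are under development, and the text expects these to help in the later trial.

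**The concern.** A prediction model can use only what is known when the decision is made. Model 1 has the shortest decision limit of the three, yet its candidates include predictors that by the protocol's own account arrive well after that limit. The criteria given (AUC, reclassification, a small number of predictors) reward discrimination whatever the time of availability.

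The study data will not expose the problem. Markers are measured later, in batches from frozen samples, so at analysis a late marker sits in the data set beside a blood pressure taken at the triage desk and looks equally usable.

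If a marker such as proADM is retained, it will share predictive weight with correlated vital signs, and stepwise or Lasso selection may drop some of those. The resulting score and its AUC describe a model that needs the marker. A triage nurse without the result could not compute it, and deleting the marker term without refitting would leave weights that belong to a different model. The protocol plans to test the derived algorithms in a later randomised trial, so it matters which version of model 1 is carried forward.

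**Working it through.** **Inputs**

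- High/low priority cut-off: 10 minutes (Endpoints). Class 2 is the 10-minute option, so high priority means a wait of at most 10 minutes.
- Other waiting limits: 30, 90 and 180 minutes (Endpoints).
- Marker time to result: 1–3 hours, that is 60–180 minutes, for most markers and for proADM by name (Potential limitations and bias).
- Expected high-priority rate: 20% of at least 5000 patients, with 10 cases per degree of freedom (Statistical considerations and sample size).

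**The plan's own figure.** 5000 × 0.20 = 1000 high-priority cases, and 1000 / 10 = 100 degrees of freedom. This reproduces the upper end of the stated 50–100. The timing point does not depend on it.

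**Turnaround against each limit.** Ratio = time to result / waiting limit.

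| Waiting limit (min) | Fastest (60 min) | Slowest (180 min) |
|---|---|---|
| 10 | 60/10 = 6 | 180/10 = 18 |
| 30 | 60/30 = 2 | 180/30 = 6 |
| 90 | 60/90 = 0.67 | 180/90 = 2 |
| 180 | 60/180 = 0.33 | 180/180 = 1 |

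Even the fastest stated result comes after both the 10- and the 30-minute limit. The 90-minute limit is exceeded over (180 − 90)/(180 − 60) = 90/120 = 75% of the width of the stated range. That is a share of the range, not of markers or patients. The 3-hour limit is never exceeded.

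**Which model 1 versions are specified.**

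1. The MTS alone: specified, and computable at triage.
2. The MTS plus clinical parameters, vital signs and blood markers, reduced by selection: specified, and computable at triage only if no late marker is retained.
3. The MTS plus triage-time variables without markers: not specified as a result or as a fallback.

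The third is the version that could be used at the triage desk whatever happens to the markers.

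**The case against.** The strongest reply is that the authors saw the delay and disclosed it as a limitation, with an answer: faster tests are coming. In a derivation study, accepting that risk is a judgement and not a contradiction. This stands as far as disclosure goes. It does not settle the matter, because the tests are only in development and marker selection does not wait for them.

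Second, model 1 is built in steps, with the MTS alone first, so a marker-free benchmark will exist. That is correct, but the MTS is the tool to be improved and not the improved tool.

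Third, the article says that candidate predictors differ between models, and the full lists may stand in documents not shown. A list by itself would be no finding. Here, however, the article itself fixes the cut-off, the time of use and markers as model 1 inputs, and these pull against each other.

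Some stronger readings are tempting but not supported:

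- *Model 1 will be unusable at triage.* Selection is data-driven and may drop every late marker.
- *Urea shares the 1–3 hour delay.* The text says most markers and names only proADM. It gives no time for urea.
- *The weights and AUC will be invalid.* This holds only if a marker is removed without refitting, and a refit is simple.
- *The marker model should become secondary.* Whether markers improve on the MTS is a central question of the Background and of the overall hypothesis. Demoting it would change a stated aim.
- *A late result is useless for everyone.* For patients who can safely wait, a result within 3 hours may still inform their priority.

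**Conclusion.** The point holds as a risk confined to model 1. Following the article as written could yield a priority score that needs an input arriving 6 to 18 times later than the cut-off it predicts, and no enhanced marker-free score is specified to take its place. Models 2 and 3 have no 10-minute limit and are not affected.

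The conclusion assumes that the stated 1–3 hours is the time to a usable result, counted from the blood draw or later, and that a late marker is retained in model 1. The second cannot be known before the data are analysed. The documents give no basis for estimating how far coefficients would shift or how much AUC would be lost without markers, so the size of the point is expressed in time only. Nothing is lost at data collection and the matter can be put right at analysis. It is a cheap improvement, best planned in advance so that the choice between versions does not follow the results.

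**What to change.** In Statistical considerations and sample size, derive and validate model 1 in two separately fitted versions:

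1. the MTS plus variables recorded at triage (vital signs, presenting complaint, age and sex);
2. the same variables plus blood markers.

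Use the planned 1:1 training and validation split for both. Report the gain in AUC and reclassification of version 2 over version 1, and state for each the time after arrival at which it can be computed. Present only version 1 as usable at the triage desk, unless the marker retained in version 2 is available within the decision time. Testing the added value of markers stays a main aim, and models 2 and 3 stay as planned.

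The cost is one extra model fit on data already collected. Version 1 draws on a subset of the candidates of version 2, so it needs no more cases. The downside is that the AUC of the triage-time version may be slightly lower than that of the version with markers.

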### Trial status

Ongoing trial with start of recruitment in June 2013 and planned termination 12 month later.

## Abbreviations

CI: Confidence interval; ED: Emergency department; ICU: Intensive care unit; LOS: Length of stay; MTS: Manchester triage system; OR: Odds ratio; PCT: Procalcitonin; ProADM: Pro-adrenomedullin; DRG: Diagnosis-related groups; SPI: Selbstpflegeindex (self care index); PACD: Post-acute care discharge score.
